### Strategies to improve adherence to interventions {11c}

Lithium blood plasma levels will be checked during each visit to ascertain therapy adherence. Patients will be phoned after they receive a dose change to improve adherence. To minimize the burden for patients, Blood samples are analyzed at the local lab and results are sent to the unblinded physicians for dose adjustment review. If a local option is not feasible, patients are requested to visit their study site.

### Relevant concomitant care permitted or prohibited during the trial {11d}

Patients taking concomitant riluzole at study entry must be on a stable dose for at least 30 days prior to the baseline visit and must continue taking the same dosage throughout the study, unless the Investigator determines that riluzole should be discontinued for medical reasons, in which case it may not be restarted. Concomitant medication for symptom management (i.e., spasms or saliva management) during the study is at the discretion of the Principal investigator. Daily intake of all concomitant vitamins and supplements should, preferably, be stabilized at least 30 days prior to the baseline visit.

If a study patient initiates Edaravone treatment during the study, the patient will be discontinued from the study treatment. Additionally, any investigational therapy being evaluated for efficacy in ALS or other diseases is prohibited beginning 30 days prior to the baseline visit and throughout the study. Use of antipsychotics (e.g., haloperidol, thioridazine, fluphenazine, chlorpromazine, olanzapine and clozapine), digoxin, calcium antagonists, carbamazepine, methyldopa, verapamil and diltiazem are prohibited during the study due to their interactions with lithium carbonate.

### Provisions for ancillary and post-trial care {30}

After completion of the 24-month follow-up period, patients will be offered to enroll in an open-label extension phase. Possible damages caused by participation in the current trial are covered by an insurance taken out by the Sponsor in accordance with legal requirements. The insurance applies to the damage that becomes apparent during the study or within 4 years after the end of the study.

### Outcomes {12}

#### Primary outcomes

The primary endpoint of this study is a composite endpoint, defined as time to death from any cause or respiratory insufficiency (tracheostomy or the use of non-invasive ventilation for ≥22 h per day for ≥10 consecutive days).

#### Secondary outcomes

Combined effect on daily functioning and overall survival based on a joint model of survival and ALSFRS-R total scores.Daily functioning, defined as mean change from baseline in ALSFRS-R total score. Disease progression will be monitored using the ALSFRS-R, which is a validated 12-item questionnaire designed to evaluate the functioning of respiratory, bulbar, fine and gross motor function in ALS patients [22]. The total score ranges from 48 (no limitation in daily activities) to 0 (total inability). The ALSFRS-R slope, the difference in scores standardized for time, is often used as measure of disease progression in clinical trials and is significantly associated with survival [23].Respiratory function, defined as mean change from baseline in Slow Vital Capacity (SVC). The SVC is associated with survival in ALS patients [24]. The obtained estimates of the vital capacity will be recorded in liters and standardized using the GLI-2012 reference standard [25].Change in outcome of Plasma creatinine. Plasma creatinine is a part of the safety tests and will be used as one of the secondary endpoints to monitor disease progression [26]. Plasma creatinine is well correlated with functional decline, muscle strength and is highly predictive for overall survival. Due to the effect of disease progression on plasma creatinine, Cystatin C will be used for monitoring kidney function as safety parameter [27].Clinical disease stage, defined as mean time spent in each stage of the King’s and ALS Milano-Torino staging systems. The King’s staging system is a simple clinical staging system, which defines four stages of ALS. The first three stages are defined by functional involvement of a region: bulbar, upper limbs and lower limbs. The number of regions involved gives the stage. Stage 4 is reached if swallowing (4A) or respiratory (4B) difficulty is severe enough to require intervention. This procedure takes the form of a semi-structured interview. MITOS is a similar clinical staging system, in which the stages are defined as loss of independence on the four domains of the ALSFRS-R: swallowing, walking/self-care, communicating and breathing [28]. Studies have shown that both King’s staging and the ALS-MITOS correlate with survival [29, 30].Safety based on the safety assessments including neurological examinations, clinical laboratory evaluations, vital signs and frequency of adverse events (AEs) or serious adverse events (SAEs). (S)AEs will be categorized according to the Common Terminology Criteria for Adverse Events and will be rated for severity and association with study drug.Tolerability defined as time-to-discontinuation of assigned treatment since randomization.Change from baseline in urinary P75^ECD^. P75 is a neutrotrophin receptor that is expressed after motor neural damage and excreted through the urine [31]. Hence, presence of P75^ECD^ in the urine is indicative for the degeneration of motor neurons. P75^ECD^ has been shown to increase over time in patients with ALS and correlates well with measures of functional decline. Moreover, the marker is associated as independent predictor of survival. Therefore, P75^ECD^ may have the utility as a potential pharmacodynamic biomarker and slowing of a rising urine level may be indicative of a biological effect.Change from baseline in plasma Neurofilament light and heavy chain. Neurofilament light and heavy chains in ALS are well known to be correlated with prognosis and remain relatively stable over time [32]. A change in the expression of neurofilament light and/or heavy chain may, therefore, be considered as supporting evidence of disease amelioration in ALS.Neuropsychological status, defined as change from baseline on the ECAS and ALS-FTD-Q. Approximately 35% of the patients, with ALS, experience cognitive or behavioral impairment. The cognitive and behavioral impairment may increase as disease progresses [33]. The neuropsychological status of patients will be evaluated using the Edinburgh Cognitive and Behavioral ALS Screen (ECAS) [34]. The ECAS is independent of motor disability and evaluates five cognitive domains: language functions, executive functions, and letter fluency, memory and visuospatial functioning. If available, ECAS version A and B will be alternated to prevent a training effect in patients. The questionnaire has a behavior screen with a carer interview, this part will not be performed in this study. In addition, we will evaluate behavioral disturbances using the ALS frontotemporal dementia questionnaire (ALS-FTD-Q) [35]. The ALS-FTD-Q is a validated instrument for the screening of behavioral disturbances in ALS. The ALS-FTD-Q has 25 items (including three cognitive items: memory, concentration, and orientation in time), with a 4-point rating scale; the maximum score is 100. A higher score indicates more behavioral disturbances.Global quality of life (QoL), defined as change from baseline on the visual analog scale (single-item scale) and EQ-5D. QoL will be measured using a visual analog scale (single-item scale): a horizontal line of 100 mm ranging from 0 (worst imaginable QoL) to 100 (perfect QoL) [36]. Generic QoL will be measured using the EQ-5D. The EQ-5D measures the health status in terms of five dimensions: mobility, self-care, usual activities, pain and depression. From the EQ-5D a quality-adjust life year (QALY) can be calculated, which is required for cost-utility analysis if a drug is beneficial for patients with ALS [37]. If a patient deceases during the follow-up period, the date will be recorded. If a patient reaches the criteria for respiratory insufficiency (tracheostomy or the use of non-invasive ventilation for ≥22 h per day for ≥10 consecutive days), the date this criterion was met will be recorded and the patient will no longer be part of the study. The time point for all secondary outcomes is month 24.

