Patients will be withdrawn from the study by the Investigator in consultation with the coordinating Investigator and the Sponsor in case of:Liver toxicity where one or more of the following criteria (in alignment with the FDA premarketing clinical liver safety guidance) are met and no compelling alternate cause is):ALT ≥ 3×ULN and bilirubin ≥2×ULN (>35% direct bilirubin)ALT ≥ 5×ULNALT ≥ 3×ULN and with symptoms believed to be related to liver injury or hypersensitivity.ALT ≥ 3× baseline ALT and with symptoms believed to be related to liver injury or hypersensitivity.Allergic reaction criteria are met and no compelling alternate cause is identified:° CTCAE Grade III/IV: severe skin reaction (Steven-Johnson syndrome, Toxic Epidermal Necrolysis or Erythema Multiforme). Patients with Grade ≥3 allergic reactions that are considered to be possibly or probably related to the investigational product should permanently discontinue the investigational product regimen and the patient should be withdrawn from the study. Patients should be treated as clinically appropriate and followed until resolution of the adverse event.° Patients may continue investigational product for CTCAE Grade I or II allergic reactions at the discretion of the Investigator. The patient should be advised to contact the Investigator immediately if there is any worsening of symptoms or if further systemic signs or symptoms develop. Antihistamines, topical corticosteroids, or antipruritic agents may be prescribed.° If a profuse, purpuric and coalescing leukocytoclastic vasculitis occurs, the patient should be withdrawn from the study.Development of moderate to severe renal impairment as measured by Cystatin C (< 50 mL/min).Note: In case of renal impairment, medication may be stopped for 2 weeks, after which the patient is retested. If the renal impairments persist, patients are withdrawn from the study.The patient becomes pregnant.Noncompliance with the protocol as judged by the investigator.

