#### Statistical methods for secondary outcomes

ICombined assessment of daily functioning and survival, defined as death from any cause [50, 51]. A joint model will be constructed between a survival model and a longitudinal model for ALSFRS-R data to evaluate the combined effect on both endpoints simultaneously; the full testing procedure is described elsewhere [52]. In short, the survival sub-model will contain treatment allocation as covariate and will be stratified for randomization factors “trial site and adjusted for “TRICALS Risk Profile” as a continuous variable, where the baseline hazard function follows a Weibull distribution [53]. A mixed effects sub-model will be fitted for the ALSFRS-R data with a random intercept and random slope for time per individual. The fixed effects part contains: baseline ALSFRS-R, treatment, time, baseline ALSFRS-R*time and treatment*time. Time will be fitted both linearly as well as non-linearly using restricted cubic splines. The non-linear effect of time will be kept in the model only if significant. If not, fixed non-linear time will be deleted first, followed by random non-linear time. An unstructured covariance matrix will be used to model the correlations among repeated measures. A likelihood ratio test will be used to compare a joint model with the treatment terms vs. a joint model without the treatment terms, thereby estimating the combined effect on both the ALSFRS-R and mortality, irrespective of their association.IIALSFRS-R scores will be analyzed using the same joint model framework outlined above to account for the informative censoring due to patient death (i.e., mortality-adjusted progression). Here, we will use a likelihood ratio test to evaluate the time*treatment interaction from the ALSFRS-R sub-model. A similar strategy will be applied for change from baseline in Predicted %SVC, plasma creatinine, and QoL.

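### Plasma creatinine is analysed as a progression marker with no kidney-function term, so a fall in renal clearance on lithium, if there is one, would look like slower progression

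*Protocol article*

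**What the plan says.** Under Secondary outcomes, the protocol article gives creatinine two roles: "Plasma creatinine is a part of the safety tests and will be used as one of the secondary endpoints to monitor disease progression". It justifies the efficacy role as follows: "Plasma creatinine is well correlated with functional decline, muscle strength and is highly predictive for overall survival". A better-preserved value therefore reads as slower disease. The same paragraph recognises that the marker carries two signals, and protects one of them: "Due to the effect of disease progression on plasma creatinine, Cystatin C will be used for monitoring kidney function as safety parameter".

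Under Statistical methods for secondary outcomes, creatinine is attached to the ALSFRS-R analysis: "A similar strategy will be applied for change from baseline in Predicted %SVC, plasma creatinine, and QoL". For ALSFRS-R that strategy is spelled out: "The fixed effects part contains: baseline ALSFRS-R, treatment, time, baseline ALSFRS-R*time and treatment*time". The tested term is also named: "we will use a likelihood ratio test to evaluate the time*treatment interaction from the ALSFRS-R sub-model". No kidney-function term appears.

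Kidney function on treatment is covered elsewhere. The eligibility criteria exclude patients below 50 mL/min at baseline, preferably judged on cystatin C, with a creatinine-based estimate allowed where cystatin C is unavailable. The criteria for discontinuing {11b} list as a reason for withdrawal: "Development of moderate to severe renal impairment as measured by Cystatin C", with the same 50 mL/min limit and a provision to stop medication and retest. General methods makes all secondary endpoints exploratory, reported with 95% confidence intervals and without inferential statements.

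**The concern.** Plasma creatinine depends on how much muscle produces it and on how fast the kidneys clear it. The protocol deals with this in one direction only: muscle loss should not mask a kidney problem, so cystatin C is used for safety. The reverse is left open, namely that a change in clearance moves the efficacy marker.

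Randomisation does not remove this. A renal effect of the study drug would arise after randomisation, in one arm only, and in a known direction: lower clearance, higher creatinine, apparently better-preserved muscle. An unwanted drug effect could then appear in the results table as a favourable estimate on a disease marker.

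**Working it through.** **The plan's own figure.** The document gives no effect size, variance or expected renal change for creatinine, so there is nothing to reproduce. The 72-event calculation concerns the primary endpoint and plays no part here.

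**Inputs from the document.** 114 patients on lithium and 57 on placebo; quarterly visits to month 24; renal withdrawal limit 50 mL/min; no renal term named in the model.

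**Assumed, not in the document.** A 5%, 10% or 15% fall in mean clearance on lithium by month 24.

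**Step 1, level.** At steady state, creatinine = generation / clearance. If generation falls by a fraction g and clearance by f, the ratio to baseline is (1 - g)/(1 - f). At fixed muscle mass (g = 0):

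| Clearance fall | Creatinine ratio | Change |
|---|---|---|
| 5% | 1/0.95 = 1.053 | +5.3% |
| 10% | 1/0.90 = 1.111 | +11.1% |
| 15% | 1/0.85 = 1.176 | +17.6% |

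With real muscle loss the decline is hidden. For g = 20% and f = 10%, 0.80/0.90 = 0.889, so a 20% loss shows as 11.1%.

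**Step 2, what the withdrawal limit leaves in.** A patient starting at 80 mL/min can lose 30/80 = 37.5% of clearance before reaching 50 mL/min. At fixed muscle mass that is 80/50 = 1.60, or creatinine +60%. Smaller falls stay in the analysis.

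**Step 3, which term is biased.** On the log scale a clearance fall adds -ln(1 - f) to creatinine.

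- Gradual and even over two years: the false slope difference is -ln(1 - f)/2 per year. This gives 0.0513/2 = 0.026, 0.1054/2 = 0.053 and 0.1625/2 = 0.081 log units per year for 5%, 10% and 15%.
- Early and then constant: the slope is unaffected, and the level shifts by about 0.05, 0.11 and 0.16 log units.

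**Step 4, what normalising does.** If cystatin C is also generation/clearance, clearance cancels in log(creatinine/cystatin C). The difference between the two generation terms is left. This needs cystatin C generation to be unaffected by muscle loss, which is the protocol's own reason for using it, and by lithium, which is an assumption.

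**Step 5, simulation check.** A simple two-stage slope analysis stood in for the joint model: 3,000 trials, 114 vs 57, complete quarterly follow-up, 20% loss of creatinine generation in both arms, between-patient log-slope SD 0.10 per year, no disease effect.

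| Clearance fall on lithium | Slope bias, gradual fall | Slope bias, early constant fall | Level shift, early constant fall | Slope bias, gradual fall, normalised |
|---|---|---|---|---|
| 5% | 0.0255 | 0.0002 | 0.0515 | -0.0001 |
| 10% | 0.0529 | 0.0002 | 0.1059 | -0.0005 |
| 15% | 0.0813 | 0.0000 | 0.1622 | -0.0001 |

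In the gradual case the 95% interval excluded zero in 30%, 86% and 99.5% of trials unadjusted, and in about 5% when normalised. The unadjusted rates should not be used to grade the point. They rest on assumed SDs and complete follow-up, whereas the Interim analyses section expects only 11.3% of patients to stay 18 months or more, and 1.8% to complete 24 months, if treatment is futile. The direction of the bias does not depend on these choices.

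**The case against.** The strongest reply is that the causal premise is missing. Nowhere does the document say that lithium lowers clearance. Renal limits sit beside liver, allergy and pregnancy criteria, and show that kidney function is watched, not that the drug reduces it. The article also describes earlier placebo-controlled trials as raising no major safety concerns. This stands, and the point is therefore conditional.

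A reader might go further and infer that the endpoint is biased toward lithium as a matter of fact, that any fall in clearance biases the planned test, or that kidney harm would be reported as evidence of efficacy. The documents support none of these. The size of any renal effect is not given. A constant early fall leaves the tested slope almost untouched. The article's remark about supporting evidence of disease amelioration concerns neurofilament, not creatinine. Cystatin C and laboratory safety data would also be available to check a suspicious result.

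It can also be said that the listed covariates belong to ALSFRS-R, that creatinine is promised only a similar strategy, and that a statistical analysis plan, not shown here, could add a renal term. That is fair, and it softens the point. It does not remove it: the published strategy names no such term, although the same article recognises that creatinine is confounded when it is read for safety.

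**Conclusion.** The point holds in conditional form. The plan protects the safety reading of creatinine from muscle loss but does not protect its efficacy reading from kidney function. If clearance fell by 5-15% on lithium, creatinine would be about 5-18% higher at fixed muscle mass without any disease effect. A progressive fall would bias the time-by-treatment slope toward lithium, by about 0.03 to 0.08 log units per year if spread evenly over 24 months. An early, stable fall would mainly shift the level of change from baseline.

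These sizes rest on the assumed clearance range and on steady state. The consequence is limited to the interpretation of one exploratory secondary marker. The primary endpoint, the 72 events and the stopping rules are untouched. The point still merits a change, because an interval shifted in the drug's favour can mislead without a formal inference and the remedy is cheap.

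**What to change.** In the creatinine analysis, prespecify a second analysis of log(creatinine/cystatin C), both from the same visit, fitted with the same model and shown beside unadjusted creatinine. Report change in cystatin C by arm. State in advance that a creatinine difference will not be interpreted as slower progression unless the cystatin C-normalised result agrees.

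Two alternatives are less suitable. Reducing creatinine to descriptive safety data would go against the article's own reasoning, which prefers cystatin C for kidney safety because disease progression affects creatinine. A time-varying cystatin C covariate as the main analysis would condition on a post-randomisation variable that treatment may affect, and so change the question being answered.

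The cost is a little more analysis work and some lost visits. Cystatin C is already the kidney-safety marker, and blood is drawn at baseline and at every quarterly visit. However, Table 1 does not list cystatin C by visit, safety assessments are evaluated locally, and the eligibility criteria accept that it may be unavailable. Missing outcomes are not imputed, so visits without it would drop out of the normalised analysis. Its availability by site should be confirmed, and the wording settled before unblinding.

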### Plans to promote participant retention and complete follow-up {18b}

As ALS progresses, patients may experience increasing difficulty to adhere to the nominal visiting schedule. To reduce discontinuations due to non-compliance, we provide an alternative monitoring option for debilitated patients, if allowed according to local laws and regulations. If, in the judgment of the principal investigator, the patient cannot reasonably be expected to travel to the clinic, the minimum data required for continued participation in the study (i.e., remain on the study medication) are laboratory tests, adverse event reporting and ALSFRS-R, all of which can be obtained remotely by a trial nurse, either during a home visit or by phone. Blood samples for safety assessments may be obtained by the patient’s general practitioner or any other local blood collection option that has been approved by the Sponsor. These data are to be obtained according to the nominal visit schedule until the patients withdraws, reaches the endpoint or the study completes, whichever comes first. If the patient becomes unfit for travel, this information will be documented in the source data. If no accommodations can be made for adequate safety monitoring, patients are withdrawn from study medication and the minimum requirement for follow-up will be assessment of survival data (i.e., living status or date of death).

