### Methods in analysis to handle protocol non-adherence and any statistical methods to handle missing data {20c}

Missing data in any of the outcomes will not be imputed.

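### Patients leave the study at respiratory insufficiency, so the first secondary outcome, as written, estimates death censored at respiratory insufficiency and not overall survival

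*Protocol article*

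**What the plan says.** The protocol article lists as its first secondary outcome: "Combined effect on daily functioning and overall survival based on a joint model of survival and ALSFRS-R total scores". Under Statistical methods for secondary outcomes, item I, the survival part is defined as death from any cause. This differs from the primary endpoint, which is "time to death from any cause or respiratory insufficiency (tracheostomy or the use of non-invasive ventilation for ≥22 h per day" for at least 10 consecutive days).

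Two statements end follow-up at RI:

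- Secondary outcomes: once the RI criterion is met, "the date this criterion was met will be recorded and the patient will no longer be part of the study".
- Section {18b}, on patients monitored remotely: data are collected "until the patients withdraws, reaches the endpoint or the study completes, whichever comes first".

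Three statements bear on the collection of deaths, and none of them covers a patient after RI:

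- Secondary outcomes, the sentence just before the RI rule: "If a patient deceases during the follow-up period, the date will be recorded".
- Table 1 schedules survival data at every visit to month 24.
- Section {18b}, for patients taken off study medication because safety monitoring cannot be arranged: "the minimum requirement for follow-up will be assessment of survival data (i.e., living status or date of death").

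On analysis, item II uses the joint model to "account for the informative censoring due to patient death". RI as a reason for censoring death is not mentioned. Section {20c} adds: "Missing data in any of the outcomes will not be imputed".

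**The concern.** A model of death from any cause needs dates of death for everyone, including patients who first reach RI. If those patients leave the study at RI, the only option left for the survival sub-model is to censor them there. This is not neutral. RI is a sign of advanced disease, and the trial treats it as equivalent to death in its primary endpoint, so patients censored at RI are unlikely to have the same later risk of death as those still under observation.

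At stake is the meaning of the first-listed secondary outcome. It would be reported as a combined effect on function and overall survival when the data describe something else. If one arm had more RI and fewer direct deaths than the other, part of that shift could look like an effect on survival.

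**Working it through.** **1. The plan's own figure.** The article gives no number for deaths, for RI or for this secondary outcome. Its only related figure is 72 events for 80% power on the composite. By Schoenfeld with 2:1 allocation, HR 0.50 and one-sided 0.025, the events needed are (1.960 + 0.842)² / [(2/3)(1/3)(ln 0.5)²] = 7.849 / 0.1068 = 73.5, so 74. At 72 events, √(72 × 2/9) × 0.693 − 1.960 = 0.813, which gives 79.2% power. The stated figure is reproduced closely. It concerns death or RI, and the RI date is recorded, so nothing here changes it.

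**2. The passages side by side.** The outcome needs deaths after RI. The RI rule removes the patient, and {18b} stops scheduled collection at the endpoint. Vital-status-only follow-up exists, but for a different group. A patient no longer in the study has no Table 1 visits, and it is at best unclear whether a later death falls within that patient's follow-up period. Imputation is excluded. As written, the estimand is death censored at RI.

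**3. Illustration of size.** All inputs below are assumptions, except that 17.7 months is the article's mean survival after diagnosis, borrowed here as a placebo median to death or RI. Hazards are constant.

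- h = ln 2 / 17.7 = 0.0392 per month; T = 24; hT = 0.940; exp(−hT) = 0.391.
- p = share of first events that are RI. Death hazard after RI = m × h.
- Estimate with censoring at RI: exp(−(1 − p)hT).
- True survival: S = exp(−hT) + [p/(m − 1)] × [exp(−hT) − exp(−mhT)]; for m = 1, exp(−hT)(1 + phT).
- Unrecorded share of deaths: 1 − (1 − p)(1 − exp(−hT)) / (1 − S).

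With p = 0.20 and m = 2, the estimate is exp(−0.752) = 0.471 and the true value is 0.391 + 0.2 × (0.391 − 0.153) = 0.438. The overstatement is 3.3 points, and 1 − 0.487/0.562 = 13% of deaths are unrecorded.

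With p = 0.20 and m = 0.5, the true value is 0.391 + 0.4 × (0.625 − 0.391) = 0.484. Survival is now understated by 1.3 points.

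The sign changes at m = 1 − p, where the death hazard after RI equals the direct-death hazard before it.

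Error in 24-month placebo survival, in percentage points (unrecorded share of deaths in brackets):

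| RI share | m = 0.5 | m = 1 | m = 2 | m = 4 |
|---|---|---|---|---|
| 5% | −0.5 (1%) | 0.0 (2%) | +0.7 (3%) | +1.3 (4%) |
| 10% | −0.8 (2%) | +0.2 (4%) | +1.5 (6%) | +2.6 (8%) |
| 20% | −1.3 (5%) | +0.7 (9%) | +3.3 (13%) | +5.6 (17%) |
| 30% | −1.3 (9%) | +1.7 (15%) | +5.6 (21%) | +9.1 (26%) |

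**4. Between-arm comparison, equal mix.** Apply HR 0.50 to every hazard, including the one after RI, with the same p in both arms. The censored-at-RI hazard ratio is 0.50. The true ratio of death rates (deaths over person-time to month 24) is 0.47 to 0.51 across the table.

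**5. Between-arm comparison, unequal mix.** Keep the composite hazard equal in both arms, with RI shares of 15% on placebo and 25% on active. The censored-at-RI ratio is (1 − 0.25)/(1 − 0.15) = 0.88. With a mean time from RI to death of 4, 8, 24 or 40 months in both arms, the true death-rate ratio is 0.97, 0.95, 0.90 or 0.88. A shift in mix can therefore appear as a survival effect, most clearly when death follows RI quickly.

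**The case against.** The strongest reply is that a clear bias is not shown. A reader might infer that overall survival is overstated, and by a large amount. With a composite median of 15 months, an RI share of 15% to 35% and a mean of 4 to 8 months from RI to death, one obtains roughly 4 to 13 points. But those inputs put the death hazard after RI at about 3 to 8 times the direct-death hazard before it, so the overstatement is built in. The article supports neither the inputs nor the sign. This part of the reply stands.

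The plan also schedules no 24-month overall survival estimate for this outcome. It specifies a between-arm likelihood ratio test, and with an equal RI mix the hazard ratio barely moves. This stands too. A differential mix in a double-blind trial is possible, but the article gives no reason to expect it.

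A reader might further infer that every outcome analysed in the joint-model framework is biased. That is not shown. For ALSFRS-R, vital capacity, creatinine and quality of life the test concerns the time-by-treatment term of the longitudinal part, and no effect on those slopes has been demonstrated. The link to ALSFRS-R, which includes respiratory items, may also absorb part of the dependence. The full testing procedure is in a cited source that is not at hand.

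Finally, collection of vital status after RI may have been condensed out of the article. That would answer a silence. Here the article states a rule that removes the patient, so the text needs correcting even if practice is different.

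**Conclusion.** The contradiction holds on the text alone and needs no outside figure. The survival part of the first secondary outcome is named overall survival, while the follow-up rule ends observation at RI. As written, the analysis estimates death censored at RI, with censoring that is probably informative.

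Size and direction are not established. Under the assumptions shown, 1% to 26% of placebo deaths by month 24 would be missing, and 24-month placebo survival would be off by about −1 to +9 points. Survival is overstated only if patients die faster after RI than before it. The treatment hazard ratio changes little unless the RI/death mix differs between arms. These figures rest on constant hazards and a plain survival model in place of the full joint model.

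The consequence is limited. The primary endpoint, the 72 events, the power and the interim rules are untouched, and General methods labels secondary endpoints exploratory, without inferential statements. It is still worth correcting now, because deaths not collected during the trial may be hard to recover later.

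**What to change.** Preferred: replace the statement that the patient leaves the study at RI with one saying that scheduled visits end, but vital status and date of death are collected until month 24 or trial end. This extends the vital-status-only follow-up that {18b} already provides for another group. Align the {18b} sentence on the end of data collection, and use these deaths in the joint model.

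If those deaths cannot be collected, define the event of the survival sub-model as the primary composite (death or RI), whose dates are already recorded, and stop calling it overall survival in Secondary outcomes and in Statistical methods for secondary outcomes.

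The first option costs a periodic vital-status check on the patients who reach RI, plus the wording changes. The second costs only wording, but gives up a separate reading of mortality.
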